### Study design and procedures

#### Study preparation, randomization, and recruitment

An overview of the study design is shown in Figs 1 and 2. Individuals are randomized in a 1:1 ratio to be invited for home-based screening for albuminuria with either a more conventional urine collection device (UCD) or a smartphone application (App). Randomization is performed by an independent clinical research organization that is unaware of the characteristics of the individuals that are assigned one of the two methods for home-based screening for albuminuria. A 4-block randomization method is used, with randomization performed in batches of 5,000 individuals. Individuals living in one household are randomized to the same group. A unique participant identification code is assigned to all participants. Due to the nature of the study and used study materials, blinding of the participants for the assigned screening method is not feasible.

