#### Home-based screening

All randomized individuals receive an invitation to participate in the home-based screening via mail, along with information on possible advantages and disadvantages of participation, and the assigned home-based screening method including test instructions. Participants are instructed to use midstream early morning void urine (EMV) for the test, and to postpone the home-based urine test in case of fever, urinary tract infection, pregnancy, menstruation, or having exercised intensively the day before. Two home-based albuminuria screening strategies are examined:

*UCD-method*. Individuals randomized to the UCD-method receive a PeeSpot UCD (Hessels+Grob B.V., Deventer, The Netherlands) [17,18]. This device consists of a holder containing a urine absorption pad in a transport tube (Fig 3). The urine absorption pad is a felt containing a dried hygroscopic polymer. Subjects hold the absorbent pad in their urine stream that absorbs approximately 1.2 ml of urine to collect a portion of urine. The participants insert the holder with the pad containing urine back into the tube, place the tube in a safety bag, and send this safety bag to a central laboratory by surface mail together with a signed informed consent form. A dried preservative in the urine absorption felt prevents bacterial growth during four days at room temperature. Participants are instructed to collect and send their urine sample on the same day, Monday through Thursday, and only during weather conditions that allow sending biosamples by mail (temperature between 0°C and 25°C). After receiving the sample in the central laboratory, the tube is centrifuged (5 minutes, 1800G) to release the urine into the tube with 100% albumin recovery. Urinary albumin and creatinine concentrations are measured by immuno-turbidimetry and enzymatically, respectively, on a cobas c502 analyzer (Roche Diagnostics, Almere, The Netherlands), with for albumin a lower limit of detection of 3 mg/L and intermediate precision of 4.2%, and for creatinine a lower limit of detection of 100 μmol/L and intermediate precision of 2.1%. ACR is reported as mg/mmol.

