### Outcomes

#### Primary outcomes

The primary outcomes are the participation rate and yield of the home-based screening, the elaborate screening, and the overall screening program (Fig 1). The outcomes will be assessed separately for each of the two home-based screening strategies. The participation rate is defined as the number of individuals completing the home-based screening, elaborate screening, and overall screening program relative to the number of invited individuals (with completion including the required confirmation tests). The yield of the home-based screening is defined as the number of individuals who test positive for albuminuria (at least two tests positive) relative to the number of participating individuals. The yield of the elaborate screening is determined as the number of participants with increased albuminuria and newly diagnosed or poorly controlled CVD or CKD risk factors (including hypertension, hypercholesterolemia, type 2 diabetes, and impaired kidney function.

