### Sample size

The sample size of this study is calculated to be able to show a 5% difference in participation rate between the two screening strategies, with assumptions based on previous data [7], including an overall participation rate for the home-based screening of 50%, 8% of the participants having elevated ACR, of which 90% will be confirmed by the confirmatory tests, and a participation rate in the elaborate screening of 90%. Adopting a power of 80% and a 2-sided alpha of 0.05, a minimum of 15.032 individuals are to be invited to participate to detect this 5% difference in participation rate between the two screening strategies. This number of individuals also allows discerning a significant difference between both screening strategies in the number of individuals with elevated albuminuria diagnosed with at least one newly discovered CKD or CVD risk factor.

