### Statistical analyses

The statistical package IBM SPSS (version 23, Armonk, NY) will be used for the analysis of the data. Baseline characteristics for continuous variables will be expressed as mean and standard deviation for continuous variables in case of normal distribution, and as median and interquartile range in case of non-normal distribution. Discrete variables will be reported as number and proportions. The primary outcomes, participation rate and yield of screening, will be compared between the two treatment strategies using the Chi-square test. Participation and completion rates will be presented for the intention-to-screen population. Yield of screening will be presented for the intention-to-screen population as well as the per-protocol population. Characteristics of participants and non-responders will be compared using univariable and multivariable logistic regression models. Cost-effectiveness will be assessed using an individual-level health state transition model (microsimulation), comparing the two screening strategies with usual care (no screening). It will be carried out from a Dutch healthcare perspective and the model will be run over the remaining lifetime. Data from literature will be used to estimate participants quality of life, costs of interventions after the elaborate screening, the efficacy of interventions to prevent CVD and CKD progression, and the costs associated with CVD and CKD events. Effectiveness will be calculated expressed in total costs and total effects (in QALYs) per screening method. Incremental effects will be calculated and the incremental cost-effectiveness ratio (ICER), will be determined, defined as incremental costs divided by incremental gain in QALYs.

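### Home-based yield is defined per participant, which does not match the planned intention-to-screen comparison of yield between the randomized arms

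*Protocol article*

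**What the plan says.** All references are to the protocol article.

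- **Point of randomization** (Study preparation, randomization, and recruitment; Home-based screening): "Individuals are randomized in a 1:1 ratio to be invited for home-based screening for albuminuria", and "All randomized individuals receive an invitation to participate in the home-based screening via mail". Allocation therefore comes before any decision to take part, and the randomized group is the invited group.
- **Participation rate** (Primary outcomes): completers of each stage "relative to the number of invited individuals (with completion including the required confirmation tests").
- **Home-based yield** (Primary outcomes): the "number of individuals who test positive for albuminuria (at least two tests positive) relative to the number of participating individuals".
- **Elaborate yield** (Primary outcomes): a number of participants with raised albuminuria and a new or poorly controlled risk factor. No denominator is given.
- **Analysis** (Statistical analyses): "participation rate and yield of screening, will be compared between the two treatment strategies using the Chi-square test". In addition, "Yield of screening will be presented for the intention-to-screen population as well as the per-protocol population".
- **Sizing** (Sample size): the trial is "calculated to be able to show a 5% difference in participation rate between the two screening strategies".

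**The concern.** The outcome definition and the analysis section do not fit together. An intention-to-screen yield keeps everyone in the arm to which they were randomized, so its denominator is all invitees. The only written definition of home-based yield divides by participants.

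Taking part is an effect of the assigned method. It is a primary outcome in its own right, and the trial is sized to find a difference in it. The two methods ask different things of people. The App method needs a smartphone, a download, an e-mail address and digital consent, while the UCD method needs a paper form and the post. Invitees are up to 80 years old, and the Discussion notes that CKD prevalence depends on age. The groups who respond may therefore differ in underlying risk of albuminuria. A Chi-square test on the per-participant ratio would mix that selection with any difference between the methods.

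What is at stake is the practical question of which strategy finds more people with confirmed albuminuria in the population invited. A per-participant ratio can show no difference when one strategy finds many more people. It can also show a difference when both find the same number.

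**Working it through.** **Inputs from the article (Sample size):** 15,032 invited, so 15,032 / 2 = 7,516 per arm at 1:1; participation 50%; target difference 5%, read here as 5 percentage points; 8% of participants with elevated ACR, of whom 90% are confirmed.

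**Inputs assumed here:** every participation split beyond 5 points, and every positivity other than 7.2%. The article gives no figures by arm.

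**The plan's own figure.** The article states no expected yield difference that could be reproduced. The 15,032 is used here only as the arm size. The standard two-proportion formula for 50% v 55% (80% power, two-sided 5%) gives 3,130 in total. That gap is a separate matter, and nothing below depends on it.

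**Step 1: yield under the article's assumptions.**
- Per participant: 0.08 × 0.90 = 7.2% (about 271 of 3,758).
- Per invited: 0.50 × 0.08 × 0.90 = 3.6% (about 271 of 7,516).

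**Step 2: how the two are linked.** Yield per invited = participation × yield per participant. The between-arm ratio per invited is therefore the participation ratio times the positivity ratio. The two versions agree only if participation is equal.

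**Step 3: test.** Two-sample z test with pooled variance, which equals the uncorrected Chi-square test:

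z = (p1 − p2) / √[p(1 − p)(1/n1 + 1/n2)]

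Worked example, 55% v 50% participation with 7.2% positivity in both arms. Per invited, p1 = 0.55 × 0.072 = 0.0396, p2 = 0.50 × 0.072 = 0.0360, pooled p = 0.0378. Then z = 0.0036 / √(0.0378 × 0.9622 × 2/7,516) = 0.0036 / 0.00311 = 1.16, so p = 0.25. Per participant, the difference is zero and p = 1.0.

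| Participation | Positivity among participants | Per participant | Per invited |
|---|---|---|---|
| 55% v 50% | 7.2% v 7.2% | p = 1.0 | 3.96% v 3.60%, p = 0.25 |
| 52.5% v 47.5% | 7.2% v 7.2% | p = 1.0 | 3.78% v 3.42%, p = 0.24 |
| 55% v 50%, extra 5 points all negative | 6.55% v 7.20% | p = 0.25 | 3.6% v 3.6%, p = 1.0 |
| 55% v 50% | 7.0% v 7.4% | p = 0.49 | 3.85% v 3.70%, p = 0.63 |
| 60% v 45% | 7.2% v 7.2% | p = 1.0 | 4.32% v 3.24%, p = 0.0005 |
| 60% v 45% | 6.0% v 8.0% | p = 0.0005 | 3.6% v 3.6%, p = 1.0 |
| 60% v 45% | 6.5% v 8.0% | p = 0.010 | 3.9% v 3.6%, p = 0.33 |

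**Reading the table.** In the 5-point rows the versions differ, and the direction can change, but neither version is significant in any of them. In the 15-point rows significance appears under one denominator and not under the other. In the last row the second arm looks significantly better per participant, while the first arm finds more people: 7,516 × 0.60 × 0.065 = 293 against 7,516 × 0.45 × 0.080 = 271.

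These calculations treat individuals as independent. Households are randomized together, so actual p-values may be somewhat larger.

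**The case against.** - **A randomized comparison is already planned.** A reader might infer that the primary yield comparison is not randomized at all. The article does not support that. It names the intention-to-screen population alongside the per-protocol one, and if intention-to-screen means all invitees, the right comparison is intended. This stands. What remains is that the written outcome definition does not match that analysis.
- **Which population is decisive may be settled elsewhere.** The article condenses a fuller protocol, and a SAP may exist. That the article does not name one version as decisive, or define the two populations, is not counted here. The point rests on what the article does fix, which is a denominator that does not fit its own intention-to-screen analysis.
- **Elaborate stage.** A reader might extend the criticism to elaborate participation and yield. The text does not show the same fault there. Participation is worded per invited individual for all stages, and elaborate yield is a count without a stated denominator.
- **The information is reported anyway.** Participation per invitee is also primary, and multiplying it by per-participant yield gives positives per invitee. True, so a careful reader could recover the answer. The planned test on the defined ratio would still be a test between self-selected groups.
- **The conflicts need assumed inputs.** Correct. The article gives no participation or prevalence by arm or age. It expects the App's direct communication to help participation, so it gives no ground for assuming that the App loses older people.
- **Positivity among those screened is a legitimate quantity.** Agreed, as a descriptive or supportive result.

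**Conclusion.** The point holds as a mismatch between definition and analysis. Home-based yield is defined on a post-randomization denominator, compared between arms as a primary outcome, and also promised for an intention-to-screen population that this denominator does not fit.

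Its size depends on how far participation differs between arms. At the article's own 5-point difference with equal 7.2% positivity, the discrepancy is modest (p = 1.0 v 0.25) and the conclusion is the same. Opposite significance, or a significant result in the reverse direction, appeared only with a larger assumed gap such as 60% v 45%. The documents do not support a claim that the two versions will conflict in this trial. They show only that the versions can.

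Severity: should-fix. The sized comparison, participation rate, is unaffected because its denominator is already the invited individuals.

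**What to change.** 1. Define the primary between-arm home-based yield as individuals with confirmed positive albuminuria divided by all randomized invitees, so that it matches the intention-to-screen population.
2. State the same denominator for elaborate and overall yield: participants with increased albuminuria and a newly diagnosed or poorly controlled risk factor, per randomized invitee. For elaborate yield this completes a definition that now has no denominator.
3. Label per-participant yield as a supportive positivity rate. Optionally, standardize it for age, sex and postal-code area. Date of birth, sex and address are supplied for the whole sample, including people who do not take part.
4. Record the change before the arms are compared. The article says that data collection is ongoing.

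The cost is wording only, and the same data are used. The change does not make yield a well-powered comparison. At 55% v 50% participation with equal positivity (z = 1.16), power per invited is about Φ(1.16 − 1.96) = 21%. A non-significant yield result should therefore be reported with its confidence interval and not read as equivalence.

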#### Secondary outcomes

As secondary outcome, the characteristics of participants and non-participants will be compared. Furthermore, the usability of the home-based screening strategies will be assessed based on user preferences, satisfaction rank, process evaluation, and usability success (measured as the percentage of people that tried to do a test and succeeded). Additionally, the GP follow-up rate will be assessed, defined as the number of participants visiting their GP after referral, relative to the number of referred individuals. In an exploratory analysis, the implementation of care by GPs will be assessed, defined as start or change of treatment (lifestyle advice or pharmacological treatment) in individuals visiting their GP after referral.

#### Cost-effectiveness

The cost-effectiveness of the screening is defined as the incremental cost-effectiveness ratio (ICER) in euros per Quality Adjusted Life Years (QALY) gained for each of the two screening strategies compared to the standard of care. The ICER will be modeled using data obtained in the study and treatment efficacy assumed from data in literature.

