**Methods:**

This investigator initiated, randomized population-based study will include 15.000 individuals aged 45–80 years, who will be randomly assigned to be invited for a home-based screening test for albuminuria with a more conventional urine collection device or an innovative smartphone application. If the test result is positive upon confirmation (i.e., elevated albuminuria), participants are invited to a central screening facility for an elaborate screening for CKD and CVD risk factors. Participants are referred to their GP for appropriate treatment, if abnormalities are found. Primary endpoints are the participation rate, yield, and cost-effectiveness of the home-based screening and elaborate screening.

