Several strengths regarding the study design can be mentioned. This is the first large-scale implementation study to prospectively investigate the participation rate, yield and cost-effectiveness of population-based screening for albuminuria for the early detection of CKD and CVD risk factors. The study uses a randomized approach, randomizing participants into one of the two screening strategies. Therefore, we can evaluate and compare both methods with respect to user-friendliness, willingness to participate, yield, and cost-effectiveness. This will allow an evidence-based choice for the most promising method for further exploration. The study design is further strengthened by the fact that albuminuria is not assessed only once in the home setting, but that confirmation tests are incorporated to reliably test whether albuminuria is elevated before participants are invited for a costly and more burdensome visit to a screening center for elaborate screening of CKD and CVD risk factors. This is in accordance with prevailing guidelines and takes variation in albuminuria into account, limiting the chance of false-positive findings [23].

To summarize, the THOMAS study is a unique investigator-initiated, population-based randomized trial that prospectively investigates the participation rate, yield and cost-effectiveness of screening for albuminuria for the early detection of CKD and CVD risk factors in the general population. By evaluating and comparing two home-based tests to assess albuminuria, insight will be provided to decide which strategy is the most promising to be explored further. Thus, the results of the THOMAS study will contribute to an improved, structured approach to the early detection of CKD and CVD risk factors.

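### The ICER is defined only against no screening, although the article says the two methods will be compared on cost-effectiveness to allow a choice between them

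*Protocol article*

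**What the plan says.** The Cost-effectiveness subsection of Outcomes defines the measure as euros per QALY "gained for each of the two screening strategies compared to the standard of care". The Statistical analyses section describes a microsimulation "comparing the two screening strategies with usual care (no screening". Both places name the same comparator, and neither names a ratio of one method against the other, a dominance ranking or a net-benefit rule.

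The same section then plans the outputs: "Effectiveness will be calculated expressed in total costs and total effects (in QALYs) per screening method". It closes with an ICER "defined as incremental costs divided by incremental gain in QALYs", this time without restating the comparator.

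On purpose, the Discussion says that because participants are randomized "we can evaluate and compare both methods with respect to user-friendliness, willingness to participate, yield, and cost-effectiveness", and adds: "This will allow an evidence-based choice for the most promising method for further exploration". The abstract gives the economic result weight: "Primary endpoints are the participation rate, yield, and cost-effectiveness of the home-based screening and elaborate screening". The body of the article lists participation rate and yield as primary outcomes and puts cost-effectiveness under its own heading.

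**The concern.** As options for one screening programme, UCD, App and no screening are mutually exclusive. Whether a method is worth having at all is answered by its ratio against no screening. Which method to prefer is answered by the extra cost and extra QALYs of one over the other. The definition covers the first question, while the Discussion also claims the second.

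A strategy can look acceptable against no screening and still be dominated by the other method, or be an expensive step up from it. The reverse also occurs: the method with the higher ratio against no screening can be the better choice at a given willingness to pay.

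The omitted contrast is also the one that randomization supports: "Individuals are randomized in a 1:1 ratio to be invited for home-based screening" with one of the two methods. Nobody is randomized to no screening, which enters only through the model. The trial's randomized data on participation and yield therefore bear most directly on UCD versus App.

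**Working it through.** **Figures in the article.** It states no cost, QALY, ICER or willingness-to-pay threshold, so there is nothing to reproduce. All inputs below are assumed, and they test only the decision logic.

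**Formulas.** Let C and E be a strategy's extra cost and extra QALYs against no screening, both positive, for a fixed number invited.

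- Ratio against no screening: R = C / E
- Step ICER of B over A: (C_B − C_A) / (E_B − E_A)
- Net monetary benefit at threshold λ: λ × E − C

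Putting C = R × E into the step ICER gives, for E_B > E_A:

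step ICER = R_B + (R_B − R_A) × E_A / (E_B − E_A)

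So when the more effective method has the higher ratio, the step ICER always exceeds both ratios. It grows without limit as the QALY difference between the methods shrinks.

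**Illustration 1: the lower ratio marks the less preferred method.**

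- A: EUR 50,000 and 5 QALYs, R = 10,000.
- B: EUR 84,000 and 7 QALYs, R = 12,000.
- Step: (84,000 − 50,000) / (7 − 5) = 34,000 / 2 = 17,000. By the second formula: 12,000 + 2,000 × 5 / 2 = 17,000.
- At λ = 20,000: A = 100,000 − 50,000 = 50,000; B = 140,000 − 84,000 = 56,000. B is preferred.
- At λ = 10,000: A = 50,000 − 50,000 = 0; B = 70,000 − 84,000 = −14,000. A is preferred.

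B is better at every threshold above 17,000, although A has the lower ratio.

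**Illustration 2: an acceptable ratio hides a poor step.**

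- A as above. B: EUR 78,750 and 5.25 QALYs, R = 15,000.
- Step: 28,750 / 0.25 = 115,000 per QALY.

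**Illustration 3: the lower ratio agrees with net benefit over a wide range.**

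- A: EUR 100 and 0.0100 QALY per invitee, R = 10,000. B: EUR 140 and 0.0110 QALY, R = 140 / 0.0110 = 12,727.
- Step: 40 / 0.0010 = 40,000.
- At λ = 20,000: A = 200 − 100 = 100; B = 220 − 140 = 80. A is preferred, and stays so up to 40,000.

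**Dominance.** If B costs slightly more than EUR 50,000 and yields slightly fewer than 5 QALYs, its ratio is just above 10,000 and looks fine alone. Yet A is both cheaper and more effective.

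**Range.** With A fixed at EUR 50,000 and 5 QALYs, B varied from 5.25 to 8 QALYs and B's ratio from 11,000 to 20,000. The step ICER then ran from about 12,700 (11,000 + 1,000 × 5 / 3) to 220,000 (20,000 + 10,000 × 5 / 0.25). Similar ratios against no screening are therefore compatible with very different answers to the choice between methods.

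**The case against.** The strongest reply is that the plan already holds what is needed. Total costs and QALYs per method come from one model, and the increment of one method over the other, with any dominance, follows by subtraction. The closing ICER sentence restricts no comparator. This stands. A reader might infer that the analysis cannot answer which method to choose, and the article does not support that.

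A reader might also infer that the trial will adopt whichever method has the lower ratio and so may pick the wrong one. No section states such a rule. The Discussion rests the choice on user-friendliness, willingness to participate and yield as well as cost-effectiveness, and it speaks of further exploration, not adoption. The risk is conditional on how the ratios are used, and Illustration 3 shows that the lower ratio often agrees with net benefit.

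Third, comparison with standard of care is not an error. The Introduction and Discussion both note that the cost-effectiveness of albuminuria screening has been questioned, and a ratio against no screening answers that directly. There is no reason to demote it.

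Fourth, a journal article may leave sensitivity analysis and the handling of uncertainty to a fuller plan that is not shown. That is accepted, and their absence is no part of this point. The reply does not reach the comparator itself, however. The article states a definition, gives its comparator twice, and then claims a use which that definition does not serve.

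**Conclusion.** The point holds as a mismatch between a stated definition and a stated aim. The named ICERs show whether each method is worthwhile against no screening. They do not by themselves show which method is preferable, which the Discussion says the comparison will help decide.

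No trial-specific size can be given. Under the assumed inputs, ratios of 11,000 to 20,000 against no screening went with step ICERs of about 12,700 to 220,000 per QALY. The conclusion does not depend on those figures. It rests on the methods being alternatives for one programme and on the cost-effectiveness comparison being meant to inform the choice, as the Discussion says. The fuller plan may already contain the missing contrast, in which case only the published definition needs to be brought into line.

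**What to change.** Keep the ICER of each method against no screening, for the question whether screening is worthwhile. Add to the Cost-effectiveness definition, and mirror in Statistical analyses, a full incremental analysis built on the planned totals per method:

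1. Order no screening, UCD and App by total cost.
2. Remove options that are dominated or extendedly dominated.
3. Report the ICER of each remaining option against the next-best one, so that the UCD-versus-App increment is explicit, or report net monetary benefit for all three at a stated threshold.

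The cost is a few lines of text and a small amount of extra analysis on outputs the model already produces. No new data, participants or model structure are needed.
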